## Abstract

**Background:**

Excess gestational weight gain (GWG) is common among women with overweight or obesity, increasing their risks for pregnancy complications, delivering a large infant, and postpartum weight retention. To date, only intensive interventions have had success and few interventions have been designed for implementation in healthcare settings.

**Methods:**

We describe the development, rationale, and methods of GLOW (GestationaL Weight Gain and Optimal Wellness), a randomized controlled trial evaluating the efficacy of a lifestyle intervention to prevent excess GWG among racially/ethnically diverse women with overweight or obesity in an integrated healthcare delivery system. Participants in Kaiser Permanente Northern California will be randomized, within 2 weeks of completing a study baseline clinic visit at 10 weeks’ gestation, to either usual medical care or a multi-component pregnancy lifestyle intervention adapted from the Diabetes Prevention Program (target *N* = 400). Informed by focus groups with patients and designed to be feasible in a clinical setting, the intervention will include 13 weekly individual sessions (11 delivered by telephone) focused on behavior change for weight management, healthy eating, physical activity, and stress management. Outcomes will be assessed in women and their infants from randomization to 12 months postpartum. The primary outcome is GWG. Secondary outcomes include changes in diet and physical activity during pregnancy and infant birthweight. Exploratory outcomes include cardiometabolic profile assessed via pregnancy blood samples and cord blood samples; and postpartum weight retention and infant anthropometrics up to 12 months of age. The trial includes systematic approaches to enhance intervention fidelity, intervention adherence, and participant retention in trial assessments.

**Discussion:**

GLOW is among few trials targeting excess GWG among diverse women with overweight or obesity in a healthcare setting, with long-term maternal and infant outcomes assessed up to 12 months after delivery. This evaluation of a multi-component intervention is designed to produce generalizable results to inform potential adoption of the intervention in clinical settings.

**Trial registration:**

ClinicalTrials.gov (NCT02130232): submitted April 30, 2014; posted May 5, 2014.

**Electronic supplementary material:**

The online version of this article (10.1186/s12884-019-2293-8) contains supplementary material, which is available to authorized users.

## Background

Exceeding the Institute of Medicine (IOM) guidelines for gestational weight gain has significant implications for women and their infants [1]. Up to 64% of women with overweight or obesity experience excess gestational weight gain (GWG) [2, 3], which elevates their risks for gestational diabetes mellitus, Cesarean delivery, postpartum weight retention, and obesity in later years [4–7], and for having an infant who is large-for-gestational age [8] and at increased risk for overweight or obesity in childhood [9].

Until recently, GWG interventions in women with overweight or obesity have had limited success [10] and few trials included diverse samples, despite excess GWG significantly impacting women across racial and ethnic groups [11]. Trials arising from the Lifestyle Interventions for Expectant Moms (LIFE-Moms) consortium now show that intensive behavioral lifestyle interventions, such as in-person counseling or in-person counseling paired with partial meal replacements, prevent excess GWG among women with overweight or obesity [12]. Still, intensive interventions may not be feasible for many women and may be difficult to implement in healthcare delivery settings. In addition, data are needed on long-term maternal and infant health outcomes beyond the immediate postpartum period [13].

Here we provide an overview of the GestationaL Weight Gain and Optimal Wellness (GLOW) randomized controlled trial. The trial compares usual medical care to a mainly telephone-based lifestyle intervention designed to be feasible in healthcare settings, which we hypothesize will prevent excess GWG among pregnant women with overweight or obesity. The primary outcome is rate of GWG per week, measured as a continuous variable and whether it meets the 2009 IOM guidelines [1]. Secondary GWG outcomes include weekly rate of GWG between study clinic visit assessments at 10 weeks’ and 32 weeks’ gestation, total GWG, and whether total GWG meets the IOM guidelines. Other secondary outcomes include changes in diet and physical activity during pregnancy and infant birthweight. Exploratory outcomes include changes in cardiometabolic markers assessed at 10 weeks’ and 32 weeks’ gestation, cardiometabolic profile in cord blood, postpartum weight retention at 6 and 12 months, and children’s anthropometrics at up to 12 months of age.

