### Outcome measures

The primary outcome is rate of GWG per week. GWG will be defined as the difference between the last measured pregnancy weight and the pre-pregnancy weight measured within 6 months prior to the LMP (or the pregnancy weight measured before 10 weeks of gestation if pre-pregnancy weight is missing), with all weights obtained from the EHR. Rate of GWG per week will be defined as GWG divided by the number of weeks between the date of the LMP and the last measured pregnancy weight. Rate of GWG per week will also be assessed as the proportion of women exceeding the 2009 IOM GWG guidelines for rate of GWG per week. The proportion of women who exceed the IOM guidelines for appropriate weekly rate of GWG up to delivery will be defined as being above the upper limit of the first trimester recommended amount (2.0 kg) plus the upper limit of the recommended weekly rate of 0.33 kg for overweight (BMI 25.0–29.9) or 0.27 kg for obesity (BMI ≥ 30.0 kg/m^2^), times the number of gestational weeks in the 2nd and 3rd trimester.

Secondary GWG outcome measures include weekly rate of GWG between study clinic visit assessments at 10 weeks’ and 32 weeks’ gestation, total GWG, whether total GWG exceeds the 2009 IOM GWG guidelines, and the proportion of women meeting the trial goal for GWG. Weekly rate of GWG between study clinic visits at 10 weeks’ and 32 weeks’ gestation will be calculated by dividing the amount of weight gained between visits by the weeks of gestation between visits. Total GWG will be calculated by subtracting pre-pregnancy weight from the last pregnancy weight. Total GWG will be categorized in relation to the 2009 IOM guidelines for GWG specific to women’s pre-pregnancy BMI, as follows: for exceeding guidelines, GWG will be greater than 11.5 kg (overweight) or 9.0 kg (obesity); for meeting guidelines, GWG will be 7–11.5 kg (overweight) or 5–9 kg (obesity); and for below guidelines, GWG will be less than 7 kg (overweight) or 5 kg (obesity). Meeting the trial goal for GWG will be defined as total GWG that does not exceed the lower limit of the IOM-recommended range: no more than 7 kg (overweight) or 5 kg (obesity).

Other secondary outcomes include changes in women’s diet (total caloric intake and percent of calories from total fat, saturated fat, and unsaturated fat) as well as physical activity (intensity and duration), which will be assessed at 10 and 32 weeks’ gestation.

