### Statistical analyses

Statistical analyses will be intent-to-treat, and will be conducted before and after adjusting for the variables used in the adaptive randomization procedure (age, pre-pregnancy BMI category, and race/ethnicity) [72]. We will use multiple linear regression models to examine the overall average difference between usual care and intervention conditions in mean rate of GWG and total GWG, as well as to examine the average differences in diet and physical activity variables and cardiometabolic biomarkers. We will use chi-squared tests and Poisson regression to compare conditions on the proportion of women exceeding IOM guidelines for weekly rate of GWG and total GWG, as well as to compare conditions on dichotomous outcomes.

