### Power and sample size

The target sample size is 400 participants, with 200 per condition. This sample size provides 80% power to detect a between-condition difference in mean weekly rate of GWG of at least .053 kg/week, assuming 10% attrition (α = .05, two-sided test; expected standard deviation = 0.18 kg/week given preliminary data). In addition, the maximum (protective effect assumed) detectable relative risk (intervention vs. usual care) of exceeding the IOM GWG guideline is 0.75 (power = .80, α = .05, two-sided test; expected proportion in the usual care condition = 59%, given preliminary data).

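### The primary outcome has two forms, each given power at the full two-sided 0.05, and no rule says which one decides the trial; if either may count, the false-positive rate is about 8%

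*Protocol article*

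**What the plan says.** All references are to the Protocol article.

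- **Background:** "The primary outcome is rate of GWG per week, measured as a continuous variable and whether it meets the 2009 IOM guidelines". The secondary outcomes are listed separately after this, so guideline status sits inside the primary outcome.
- **Outcome measures:** this section opens with "The primary outcome is rate of GWG per week" and then adds "Rate of GWG per week will also be assessed as the proportion of women exceeding the 2009 IOM GWG guidelines". The secondary weight-gain measures start only in the next paragraph. Background speaks of meeting the guideline, but the operational definition here is exceeding it, and I use that.
- **Power and sample size:** with 400 women and 10% attrition there is 80% power for a difference of .053 kg/week ("α = .05, two-sided test; expected standard deviation = 0.18 kg/week given preliminary data"). In addition, a relative risk of 0.75 for exceeding the IOM guideline is detectable ("power = .80, α = .05, two-sided test; expected proportion in the usual care condition = 59%, given preliminary data").
- **Statistical analyses:** linear regression is planned for the mean rate. For the binary form, "We will use chi-squared tests and Poisson regression to compare conditions on the proportion of women exceeding IOM guidelines for weekly rate of GWG". All analyses "will be conducted before and after adjusting for the variables used in the adaptive randomization procedure".

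No section names a decisive form, a testing order, a division of alpha or a requirement that both forms succeed.

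**The concern.** A mean difference and a proportion above a threshold can disagree, even when both come from the same weights. If one is significant and the other is not, the protocol does not say whether the trial succeeded, and the choice could be made after the results are known. Each form is given the full 0.05, so that figure is the error rate of each test taken alone. It is the error rate of the primary conclusion only if one form is fixed in advance as decisive.

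**Working it through.** **1. The plan's own figures.** Ten per cent attrition from 200 per arm leaves 180.

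- Continuous form: SE = 0.18 × √(2/180) = 0.01897. Then 0.053/0.01897 − 1.960 = 0.833, and Φ(0.833) = 0.798.
- Binary form: 0.59 × 0.75 = 0.4425, a difference of 0.1475 with pooled proportion 0.51625. The null SE is √(2 × 0.51625 × 0.48375/180) = 0.0527. The alternative SE is √((0.59 × 0.41 + 0.4425 × 0.5575)/180) = 0.0521. Then (0.1475 − 1.960 × 0.0527)/0.0521 ≈ 0.849, and Φ(0.849) = 0.802.

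Both reproduce the stated 80%, and each uses a full two-sided 0.05.

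**2. Correlation between the two tests.** If the rate is roughly normal and 59% of women lie above the cut, the correlation between the rate and its dichotomised version is φ(z)/√(p(1 − p)), with p = 0.59 and z the matching normal quantile. This gives 0.790. The two test statistics share this correlation under the null. It rests on two assumptions: that the 59% refers to the weekly-rate guideline, and that a single cut is an adequate approximation. The real cut varies with BMI class and gestational age, so a range is shown.

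**3. Chance that at least one form is significant under the null.** This is 1 − P(|Z₁| < 1.96 and |Z₂| < 1.96) for a bivariate normal pair:

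| Correlation | Either significant |
|---|---|
| 0 (ceiling) | 9.75% |
| 0.60 | 8.8% |
| 0.70 | 8.4% |
| 0.79 | 7.9% |
| 0.85 | 7.5% |

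If both forms had to be significant, the rate at 0.79 would be 5% + 5% − 7.9% = 2.1%.

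**4. Does running unadjusted and adjusted analyses add to this?** The adaptive randomisation balances on age, BMI class and race/ethnicity, which are also the adjustment variables. A null simulation of 360 women used minimisation on those three factors (medical center left out) and 5,000 runs per setting. The covariate mix, the gestational-age spread and the share of variance explained (R²) were assumed.

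| Assumed R² | Two adjusted tests, either | All four tests, any |
|---|---|---|
| 0.05 | 7.9% | 8.0% |
| 0.10 | 8.1% | 8.2% |
| 0.20 | 7.9% | 8.0% |

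The unadjusted tests add no more than 0.1 point to the adjusted pair. Balanced allocation makes the unadjusted continuous test conservative: it rejected in 4.5%, 4.0% and 2.8% of runs at the three settings.

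**5. After a change.** One named test gives 5%. Keeping both forms as alternative routes to success at 0.025 each holds the error to at most 5% (4.1% at correlation 0.79), but power falls to about 71% for each form.

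**The case against.** **The either-wins rule is not in the document.** A reader might infer that the plan as written treats any significant result as success, so that its type I error simply is 8% or more. The text does not say this. It is silent on the rule, and a both-must-succeed reading would give 2.1%. The 8% is therefore conditional. What stands is that the reader cannot tell which rule applies.

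**The text leans towards the continuous form.** Outcome measures names the rate first and in the singular, and the power section presents the relative risk as an additional detectable effect. That is a fair point, but order of mention is not a decision rule, and Background places both forms inside the primary outcome.

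**The 59% may not be the rate guideline.** The power section speaks only of the IOM guideline, and exceeding the total-gain guideline is a separate secondary outcome. This is correct. It affects the correlation, which is why a range is given, but not the absence of a rule.

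**Adjusted against unadjusted, chi-squared against Poisson.** A reader might count these as further chances and reach 9.6% to 11.0% for any of four tests (R² of 0.05 to 0.20). Those figures arise only under simple randomisation, which this trial does not use. Chi-squared and Poisson regression address the same proportion, and an unadjusted test alongside an adjusted relative risk is a natural reading. The choice between such models is commonly left to the statistical analysis plan.

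**The analysis plan may set a hierarchy.** It may. But the definition of the primary outcome belongs to the protocol, and here the protocol gives it two forms.

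**Conclusion.** The concern holds for the two forms of the primary outcome and goes no further. The protocol puts a continuous and a binary form inside the primary outcome, gives power at the full 0.05 for a mean difference and for exceeding the IOM guideline, and does not say which decides. If a significant result on either form were reported as a positive primary result, the error rate would be about 8% (7.9% at correlation 0.79; 7.5% to 8.8% over 0.85 to 0.60). That rests on the either-wins reading, on the 59% referring to the weekly-rate guideline, and on approximate normality of the rate. The unadjusted and adjusted analyses do not raise it materially under this trial's allocation. The power figures themselves are correct. Severity: should be fixed. The inflation is moderate and conditional, but it concerns the trial's main conclusion.

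**What to change.** State in Background, Outcome measures and Statistical analyses that the single primary test is the linear regression of the continuous weekly rate of gestational weight gain, adjusted for the randomisation variables, at two-sided 0.05. List those variables once: Consent and randomization also balances within medical center, which the adjustment list in Statistical analyses omits. Make the proportion exceeding the IOM weekly-rate guideline the first secondary outcome, tested only if the primary test is significant. Describe unadjusted results as supportive. In the power section, say which IOM guideline the 59% and the relative risk of 0.75 refer to.

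The cost is wording. The stated 80% power on the continuous outcome is unchanged and no more women are needed. The one real concession is that the binary result becomes a gated secondary claim, which cannot be made if the continuous test fails. Splitting alpha equally between the forms would avoid that gate, at the price of power falling to about 71% for each.

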## Methods

GLOW is a two-arm, parallel group randomized controlled trial testing the efficacy of a multi-component pregnancy lifestyle intervention adapted from the Diabetes Prevention Program (DPP) [14] and delivered primarily via telemedicine, as compared to usual medical care. GLOW is funded by the National Institutes of Health (R01 HD073572; PI: [name]); registered at ClinicalTrials.gov (NCT02130232; submitted April 30, 2014, posted May 5, 2014); and approved by the Kaiser Foundation Research Institute Human Subjects Committee. This article follows the SPIRIT (Standard Protocol Items: Recommendations for Interventional Trials) guidelines for reporting clinical trial protocols [15]. The sequence of trial activities for participant enrollment, intervention, and assessment appears in Fig. 1.

**Fig. 1 Fig1:**
[figure not shown]
Sequence of participant enrollment, intervention, and assessment activities: The GLOW trial

### Setting

GLOW will be conducted within Kaiser Permanente Northern California (KPNC), a large pre-paid, integrated healthcare delivery system serving over 4 million members broadly representative of the population in the underlying geographic area [16]. GLOW will recruit pregnant women from four medical centers, in Oakland, San Leandro, Santa Clara/Fremont, and Walnut Creek. These medical centers were selected based on their racial/ethnic diversity and high volume of deliveries.

### Eligibility and recruitment

GLOW aims to recruit a racially and ethnically diverse group of 400 participants to increase generalizability. Pregnant women receiving care at the selected medical centers will be first identified in the electronic health record (EHR) system. Only those < 8 weeks’ gestational age will be evaluated to confirm eligibility criteria: ≥18 years of age, pre-pregnancy body mass index (BMI) between 25 and 40 kg/m^2^ (based on weight measured in the clinical setting within 6 months before the last menstrual period), and a singleton pregnancy. Eligibility will be further assessed through a tiered process beginning with approval from medical providers to contact each patient, and EHR review. Medical exclusion criteria that may impact dietary and/or outcome assessment will be determined through the EHR review and a recruitment screening call. These include being pregnant with multiples; pregnancy loss; fertility-assisted pregnancy; diagnosed with diabetes before pregnancy; current gestational diabetes (although those diagnosed with gestational diabetes after randomization remain in the study); current uncontrolled hypertension; thyroid disease diagnosed in last 30 days; history of cardiovascular disease, cancer, lung disease or serious gastrointestinal disease; history of eating disorder or bariatric surgery; serious mental illness; recent history of mood or anxiety disorder; and drug or alcohol use disorder. Exclusion criteria that may interfere with full participation in the trial will be assessed starting at the recruitment call. These include extensive travel plans during pregnancy; plans to move out of the area or to become pregnant in the year after delivery; not having reliable transportation or telephone access; inability to communicate in English; disinterest in being randomized; and currently being over 13 weeks of gestation.

At the recruitment call, women will be asked to verify their pre-pregnancy weight as assessed in the EHR, since this measured weight will be used to calculate the GWG outcomes for all women in the trial; and for GWG goal setting for those randomized to the intervention condition. Women with a discrepancy of > 5 lbs. between the pre-pregnancy weight assessed in the EHR and by self-report will not be considered eligible to participate in the baseline clinic visit.

### Consent and randomization

Trained research assistants will obtain informed consent at the baseline clinic visit at 10 weeks’ gestation. Following this visit, women will complete at least two of three 24-h diet recalls by telephone within one week. Women will also wear an accelerometer for at least 10 h a day over at least four out of seven days (described below in section 2.6.). Women who complete fewer than two diet recalls or provide fewer than four 10-h days of accelerometer data will not be eligible for randomization. Women will also no longer be eligible for randomization if they experience a pregnancy loss between the baseline clinic visit and the time of randomization. Women with a pregnancy loss after randomization will be withdrawn from the study.

Eligible women who consent and complete the baseline assessment will be randomly assigned to either the usual care or intervention conditions. To generate each participant’s random assignment, unblinded study staff will use MinimPy, a free open-source computerized randomization program [17]. The adaptive randomization procedure is designed to ensure that equal numbers of patients are assigned to each study condition and that the two conditions remain balanced overall, within each medical center, and on each level of key characteristics: age (< 30 and ≥ 30 years), pre-gravid BMI (< 30, 30–34.9, and ≥ 35 kg/m^2^), and race/ethnicity (Asian/Pacific Islander; Black; Latina; White; and multiethnic/other/unknown). The process cannot be manipulated by study personnel. The assignment will be recorded in a Microsoft Access tracking database, where it is only accessible to non-blinded personnel (e.g., lifestyle coaches). The research assistants conducting data collection, study investigators, biostatistician, and programmer analyst will be blinded to condition assignment.

Steps taken to ensure the confidentiality of information about prospective and enrolled participants will include keeping all study information in a secured computer system used only for research, and identifying participants by a unique study identification number rather than name or medical record number. No information from the study will be placed in participants’ medical records or shared with the Kaiser Foundation Health Plan.

### Usual care

Women randomized to the usual care condition will receive standard KPNC prenatal medical care. This includes an initial prenatal visit at 7–10 weeks’ gestation; an additional 7 routine prenatal visits between 16 weeks’ gestation and delivery; and periodic health education newsletters, which include the IOM GWG guidelines and advice on healthy eating and activity in pregnancy. Medical staff routinely weigh patients at each prenatal visit.

### Lifestyle intervention

In addition to usual care as described above, women randomized to the intervention condition will receive a multi-component pregnancy lifestyle intervention called “Getting in Balance.” The Getting in Balance intervention was adapted from the DPP [14] and our prior research [18, 19] to be feasible among pregnant women for possible adoption in a healthcare system setting. The intervention targets behavior changes for weight management, healthy eating, physical activity, and stress management to meet a trial goal of gaining at the lower limit of the IOM-recommended range for GWG: 7 kg for women with overweight (BMI 25.0–29.9 kg/m^2^) and 5 kg for women with obesity (BMI ≥ 30.0 kg/m^2^).

